### Study stopping rules

An ad interim analysis will be done at the achievement of 50% of the study power (120 patients in total). The study will be stopped only in case of an increase over 30% of the median CCI in either groups. Study will be stopped immediately in case death or, a life-threatening experience (that is, immediate risk of dying) related to the use of PN, or a persistent or significant disability/incapacity will exceed 5% of the enrolled population. A Data and Safety Monitoring Board will oversee and monitor the trial to ensure participant safety and the validity and integrity of the data.

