## Outcomes

The primary endpoint of the trial is the complication burden within 90 days after surgery. The complication burden will be assessed by the Comprehensive Complication Index (CCI) (15), that incorporates all complications and their severity as defined by the Clavien-Dindo classification, and summarizes postoperative morbidity with a numerical scale ranging from 0 (no complication) to 100 (death).

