## Statistical planning

The sample size of 120 patients per group is necessary to provide an 80% power to detect at least a 30% reduction in the CCI, which is expected to be around 23 (median) (IQR 21–31) or mean 27 (±20 SD) in complicated patients of the control group. The hypothesized reduction of 30% is based on sound clinical relevance meaning that such reduction will have a consistent and significant impact of the postoperative course with advantages on well-being, quality of life, shorter length of hospitalization and a relevant reduction of heath care burden and resources. The median CCI of 23 is retrieved from a previous publication (20). The rate of complication in this type of surgery is expected to be approximately of 60%.

A Mann–Whitney test is considered, type I error rate is fixed at 5% (two tails) and an expected drop-out of 10% is taken into account.

For the binary end-points, the relative risk (RR) with the corresponding 95% confidence interval, comparing the two groups, will be estimated. For the primary end-point, also the risk difference (RD) will be computed. For the numerical end-points the difference in the location parameter (i.e., median pairwise difference) between the two groups with the corresponding 95% confidence interval will be computed. Fisher test and Mann–Whitney test will be adopted to evaluate univariate associations. Incidence of complications over time in the two groups will be described according to the Nelson-Aalen cumulative hazard estimator also accounting for multiple events per patient. The incidence in the two groups will also be compared by computing the incidence rate ratio (with 95% confidence interval). This analysis will be performed both considering all complications and only major complications.

A multivariate quantile regression model (focused on median, 25^th^ and 75^th^ percentiles) will be used to identify factors associated with the primary endpoint and to evaluate the effect of treatment adjusting for possible residual confounding. Logistic regression will also be used to model the probability of CCI >23. Using these regression models, the effect of PN over controls on the CCI will be also investigated within pre-specified subgroups to account for possible effect modification. The pre-specified risk factors for this analysis will be:

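### The interim rule on median CCI names no comparator: read between arms it contains the planned benefit, and read against the planning median of 23 an all-patient median would almost never reach it

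*Protocol article*

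**What the plan says.** Study stopping rules sets one interim look: "An ad interim analysis will be done at the achievement of 50% of the study power (120 patients in total"). The CCI criterion follows: "The study will be stopped only in case of an increase over 30% of the median CCI in either groups". No test, confidence limit or alpha is attached to it. A separate rule on deaths and life-threatening events is not at issue here.

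Statistical planning gives the design effect: "The sample size of 120 patients per group is necessary to provide an 80% power to detect at least a 30% reduction in the CCI". That CCI is "expected to be around 23 (median) (IQR 21–31) or mean 27 (±20 SD) in complicated patients of the control group". On the share of patients with complications it says: "The rate of complication in this type of surgery is expected to be approximately of 60" per cent. For the primary test, "type I error rate is fixed at 5% (two tails").

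Outcomes defines an index that "summarizes postoperative morbidity with a numerical scale ranging from 0 (no complication) to 100 (death"). A patient without complications therefore has a CCI of 0 and belongs to the endpoint.

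**The concern.** Three things about the rule are open: the reference for the increase, the direction, and the population in which the median is taken. With two randomised arms and a criterion that applies to either of them, the natural reading is that one arm's median exceeds the other's by more than 30%. That rule is symmetric. A control arm that is worse because PN works triggers it just as harm from PN would. It is also a raw ratio of two sample medians from about 60 patients each, with no allowance for sampling error.

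At stake is whether the trial reaches its planned size. A stop at 120 patients would leave an estimate from half the sample, whether the cause was a real benefit or chance. If the rule instead refers to the planning value, the question is whether it protects patients at all.

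**Working it through.** **Inputs.** From Statistical planning: 120 per group, 80% power, 30% reduction, two-sided 5%, Mann-Whitney test, 10% drop-out; control CCI in complicated patients with median 23, IQR 21-31, or mean 27, SD 20; 60% complicated. From Outcomes: CCI = 0 without complications. From Study stopping rules: 120 patients at the look, so 60 per arm, or 60 × 0.9 = 54 after drop-out.

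**The plan's own figure.** A 30% reduction of a mean of 27 is 8.1. Then n = 2 × (1.96 + 0.8416)² × 20² / 8.1² = 95.7, i.e. 96 per arm. With the usual 15% allowance for a rank test this is 110.4, and 110.4 / 0.9 = 122.7. That is within 3% of the stated 120, so the effect is understood as planned. The stopping rule has no stated operating figure to reproduce.

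**Step 1: arithmetic, between-arm reading.** If every PN score is 0.70 times its control counterpart, control/PN = 1/0.7 = 1.43. The control median is 43% above the PN median, and the trigger is 30%. The planned effect lies inside the stopping region.

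**Step 2: where the all-patient median falls.** With 40% of patients at 0, the overall median is the (0.50 - 0.40)/0.60 = 17th percentile of the complicated scores, below the stated lower quartile of 21. Sample medians are unstable there, and in about 4-5% of arms the median is 0, where a percentage increase is undefined.

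**Step 3: how often the rule fires.** Simulated at 54 or 60 per arm, stop if either median exceeds 1.3 times the other. Complicated scores were drawn from shapes fitted to the mean/SD (lognormal, gamma) or to the median and IQR (lognormal, piecewise, discrete).

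| Truth | Median in all patients | Median in complicated patients only |
|---|---|---|
| PN lowers severity by 30% | 70-95% (control arm higher in 56-85%) | 65-87% |
| PN lowers the complication rate from 60% to 42% | 89-95% | depends on shape; not a severity effect |
| No effect | 24-71% | 0.2-29% |

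Most results for the planned severity effect lie between 65% and 90%; the highest come from the discrete shapes. With no effect and all patients counted, the results by shape are 24-27% (lognormal on the IQR), 29-65% (discrete), 53-54% (piecewise), 54-57% (lognormal on mean/SD) and 69-71% (gamma). Tighter shapes go down to about 15%. With complicated patients only, shapes on the stated IQR give about 0.2-1.4% and shapes on the stated mean/SD about 18-29%.

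**Step 4: reading against the planning value.** The trigger is 23 × 1.3 = 29.9. The all-patient median is below 21. If PN raised every score by 30% it would still be below 21 × 1.3 = 27.3. The simulated firing rate is about 0%, with or without that harm. With complicated patients only, the rule fires in at most about 8-11% of trials when there is no effect.

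**Step 5: what a stop costs.** With difference 8.1 and SD 20, power at 60 per arm is Φ(8.1/(20 × √(2/60)) - 1.96) = Φ(0.26) = 0.60, and at 54 per arm Φ(0.14) = 0.56, before any allowance for the rank test. The plan promises 80%.

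**The case against.** The strongest reply is that the comparator is not named. The only median CCI the article gives is the planning value of 23, so an increase in either group may mean that either arm does worse than expected. The section also introduces a Data and Safety Monitoring Board to protect participants, which suggests a safety check and not an efficacy rule. This stands to the extent that a reader may not take early stopping of a successful trial as a certain consequence of the text. It does not rescue the rule, because an all-patient median would almost never reach 29.9. The reading is more workable with complicated patients only: a true 30% rise from 23 puts the median exactly on the trigger, so about an even chance of firing. But the section does not restrict the median in that way, and the endpoint includes the zeros.

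Three stronger inferences are tempting and are not supported:

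- *The rule usually fires by chance.* This needs the between-arm reading and an all-patient median, and the size rests on a lower tail that the article does not describe. With complicated patients only and the stated IQR, chance firing is near zero.
- *The final 5% test is badly inflated.* No interim test or efficacy claim is stated. If a stopped trial were tested at 5%, simulations gave a type I error of about 4.9-6.7%, which is small and conditional.
- *Equating 120 patients with half the study power is an error of substance.* It is half the sample, where power is about 0.56-0.60, but the number of patients is fixed in the same sentence, so nothing in the conduct changes.

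It may also be said that a full protocol or analysis plan could define the comparator. But the article does not leave the rule out. It states one, and says the study is to be stopped on it alone.

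**Conclusion.** The concern holds in this form: the CCI stopping criterion leaves comparator, direction and population open, and neither main reading gives a sound rule for the endpoint as defined. Between arms, the planned effect lies inside the stopping region. That part is pure arithmetic (1.43 against 1.30) and does not depend on any assumed shape. The sizes do: stopping in roughly 65-90% of trials in which PN lowers severity as planned, and by chance in about 15-70% (all patients) or 0-29% (complicated only) when PN has no effect. The ranges are wide because the stated IQR of 21-31 and SD of 20 imply different spreads. Against the planning value of 23, the all-patient median stays below the trigger even under a 30% rise in severity, so the rule could not detect harm. This should be corrected before the interim look. Type I inflation and the wording about study power are not grounds for the change.

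**What to change.** Rewrite the CCI criterion in Study stopping rules so that it is consistent with the planned effect in Statistical planning:

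- Remove the reference to either group and the raw ratio of medians.
- State a one-directional rule (PN worse than control) in all randomised patients with 90-day CCI at the look.
- Base it on the primary rank comparison with a pre-specified boundary. Report the chance of stopping under no effect, the planned benefit and a stated harm. The monitoring board chooses the boundary from those figures. A threshold of p<0.001 should not be taken by default: at 60 per arm it stopped in only about 0.3-6% of simulated trials with a true 30% increase in severity.
- State that there is no efficacy stop, so the final test stays at 5%. If an efficacy stop is wanted, give an alpha-spending boundary and the matching final level.

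The cost is one paragraph in the protocol and the monitoring board charter, and a short simulation. No extra patients or data are needed.

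### The interim CCI criterion rests on the median, which is nearly insensitive to excess deaths; the separate 5% clause only partly fills the gap because it compares no arms

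*Protocol article*

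**What the plan says.** All the rules stand in the section Study stopping rules of the protocol article.

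- Timing: "An ad interim analysis will be done at the achievement of 50% of the study power (120 patients in total").
- CCI criterion: "The study will be stopped only in case of an increase over 30% of the median CCI in either groups". Neither the comparator (the other arm, or the planning value of 23) nor the population (all patients, or complicated patients only) is named.
- Separate clause: "Study will be stopped immediately in case death or, a life-threatening experience (that is, immediate risk of dying) related to the use of PN", or persistent disability, "will exceed 5% of the enrolled population". The wording leaves open whether relation to PN qualifies death or only the life-threatening experience. The denominator is everyone enrolled, so the arms are pooled.
- Oversight: "A Data and Safety Monitoring Board will oversee and monitor the trial to ensure participant safety".

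The Outcomes section puts the CCI on a "numerical scale ranging from 0 (no complication) to 100 (death"). Statistical planning gives the CCI as "expected to be around 23 (median) (IQR 21–31) or mean 27 (±20 SD) in complicated patients of the control group", with a complication rate of about 60%. Mortality at 90 days is a secondary outcome and is recorded in the case report form. No expected mortality is given.

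**The concern.** The CCI gives death its maximum score, but a median uses only whether a value lies above or below the middle. A patient who dies counts no more than one with a moderate complication. With about 40% of patients at CCI 0, the all-patient median falls in the lower part of the complicated patients' distribution, far from the tail where deaths sit. Extra deaths on PN therefore shift it a little and mostly leave it below a 30% rise.

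As written, this is the only criterion at the interim look that could compare the arms. If it barely separates a trial with excess PN deaths from one without, the DSMB gets little guidance from it on the most serious outcome.

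**Working it through.** **Inputs from the article:** 60% complicated; complicated quartiles 21/23/31, mean 27, SD 20; death = 100; 1:1 allocation. The planned total is 2 × 120 = 240, so the look at 120 is half the sample, about 60 per arm.

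**Assumptions:** control 90-day mortality 3%; lowest complicated CCI 9; survivors' complicated CCI piecewise linear through the quartiles, to 50 at the 95th percentile and 70 at most; deaths fall evenly over patients. The rule is read first as PN median > 1.3 × control median, all patients.

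**Does the assumed curve fit the plan?** Segment midpoints weighted by share: 0.25×15 + 0.25×22 + 0.25×27 + 0.20×40.5 + 0.05×60 = 27.1, against the plan's mean of 27.

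**True medians.** With mortality d the median m solves (1−d)(0.4 + 0.6F(m)) = 0.5, so F = (0.5/(1−d) − 0.4)/0.6.

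- d = 3%: F = (0.5155 − 0.4)/0.6 = 0.192; m = 9 + 12 × 0.192/0.25 = 18.2.
- d = 10%: F = (0.5556 − 0.4)/0.6 = 0.259; m = 21 + 2 × 0.009/0.25 = 21.1, a rise of 16%.
- d = 15%: F = 0.314; m = 21.5, a rise of 18%.

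At 10% mortality the rise is about 7% if the lowest complicated CCI is 15, and reaches 30% only if it is 0.

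**True means.** (1−d) × 0.6 × 27.1 + 100d gives 18.8 at 3% and 24.6 at 10%, a rise of 31%. The mean reacts to the same deaths.

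**Chance of firing, 60 per arm, control mortality 3%** (simulation; the pooled clause is also confirmed by exact binomial calculation):

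| PN mortality | Median rule | 5% clause, all-cause and pooled | Deaths or mean CCI, one-sided 0.05 each | Same, one-sided 0.01 each |
|---|---|---|---|---|
| 3% | 0.22 | 0.07 | 0.05 | 0.01 |
| 9% | 0.28 | 0.59 | 0.36 | 0.13 |
| 10% | 0.29 | 0.67 | 0.43 | 0.18 |

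The last two columns use Fisher's test on deaths and Welch's test on mean CCI, firing if either crosses.

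**Other readings and shapes.** Three shapes for complicated CCI were tried (piecewise, lumpy discrete, lognormal with mean 27 and SD 20), with extra deaths falling either among complicated patients or among any. The table gives the share of trials whose median-based decision changes when PN mortality triples:

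| Reading | 2% to 6% | 3% to 9% | 5% to 15% |
|---|---|---|---|
| All patients, PN > 1.3 × control | 1–7% | 1–11% | 3–20% |
| Complicated only, PN > 1.3 × control | 2–8% | 5–14% | 15–32% |
| Complicated only, PN > 1.3 × 23 = 29.9 | 2–5% | 6–13% | 23–38% |

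With all patients and the fixed 29.9, the rule practically never fires at 3% to 9%. If a rise in either arm over the other counts, it fires in 40–55% of trials with no excess harm at all.

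**The 5% clause.** 5% of 120 is 6, so 7 events are needed.

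- 6 PN deaths against 0 is exactly 5.0% and does not exceed the limit, although two-sided Fisher p = 0.027.
- 7 control deaths against 0 on PN is 7/120 = 5.8% and would stop the trial.
- If only PN-related deaths count, then even with every PN-arm death so attributed, the chance of at least 7 at 9% mortality is 0.29.

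**The case against.** The strongest reply is that the section already has a death rule. A reader might infer from the median's weakness that even a tripling of mortality on PN would seldom stop the trial. The documents do not support that. On an all-cause, pooled reading the 5% clause fires in 0.59 of trials at 9% against 3%, and in 0.67 at 10% against 3%, more often than the between-arm tests above. It is also worded as immediate, not confined to one look. This stands, and it limits the point to the median criterion. The clause still has no direction, can miss a clear imbalance, and on its narrower reading depends on attributing each death to PN in an open-label trial.

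Second, a strict boundary would be a poor replacement. At one-sided 0.01 the two tests detect only 13–18%, and even 10 against 2 deaths among 120 per arm (one-sided p = 0.017) would not cross it. This also stands, so the boundary must be chosen on its performance.

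Third, baseline mortality is not in the article and the size depends on it. True: at 5% rising to 15% the median-based decision changes in up to 20% of trials (all patients) or 38% (complicated only).

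Fourth, between-arm review of deaths may sit in a DSMB charter that is not shown. That is possible, and the word only cannot be read as barring the DSMB from acting on deaths, since the next sentence adds another ground for stopping. But the point is not that a detail is absent. The article fixes a statistic and a threshold for this look, and that choice is poor.

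**Conclusion.** The point holds for the interim CCI criterion. Under the stated assumptions it fires in about 22% of trials with equal mortality and 28–29% at 9–10% PN mortality against 3%, so it hardly distinguishes harm from no harm. The size rests on the assumed 3% control mortality, the assumed lowest complicated CCI and the all-patient, arm-against-arm reading. At baselines of 2–3%, the other PN-worse readings give the same picture.

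It does not hold for the stopping section as a whole, because the 5% clause may well act on excess deaths. That clause is a partial safeguard of unclear scope, not a comparison of arms. The change is worth making but is not critical.

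**What to change.** - At the 120-patient look, base the harm comparison on 90-day deaths by arm and on the difference in mean CCI, both in the direction of PN being worse, in place of the median.
- Have the DSMB set the boundary in advance, after checking false alarms and detection over a range of control mortality. As a guide, one-sided 0.05 on either measure gives about 5% false alarms and 36–43% detection at 9–10% against 3%.
- Keep the 5% clause, and state whether its deaths are all-cause or PN-related.
- Reconcile the sentence that allows stopping only for the CCI with the next one, which requires immediate stopping on other grounds.

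The cost is wording in the protocol and DSMB charter; the data are already collected. The small downside is two interim harm comparisons instead of one.

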## Data collection and management

All data will be collected into an electronic database with a double entry to assure consistency of records. In case of missing or implausible data, queries will be mailed to the participating centers to obtain integrations or corrections. Data collectors will be blinded to allocation.

The patient first and last name and date of birth will be omitted according to the Italian legislation on privacy. Subject identification will be carried out only by the randomization code.

All data will be collected into a dedicated excel spreadsheet. This electronic registry will be identical for all centers and each center will have their own dataset. The excel spreadsheet will be protected by a password possessed by the assessor.

### Case report form

The following baseline patient-related parameters will be recorded:

- Age (years)- Sex- Weight (kg)- Height (m)- Body mass index (kg/m^2^)- Nutritional risk score-2002- Percent of weight loss in the 6 months prior to surgery- Charlson comorbidity index- Diabetes- Jaundice- Biliary stenting- Routine laboratory test (albumin, preabumin, bilirubin, hemoglobin, creatinine, HbA1c, CRP)- Primary disease with indication to surgical resection- ASA score- Neoadjuvant treatments

The following intraoperative parameters and events will be recorded:

- The day of operation- Type of surgical procedure (PPPD, Whipple)- Type of pancreatic anastomosis (gastric, jejunal)- The level of intraoperative contamination (clean; clean-contaminated; contaminated; dirty)- Use of epidural analgesia, TAP block, subfascial catheter- Intraoperative hypothermia (defined as body temperature < 35.5°C for more than 30 min)- Estimated blood loss (mL)- Volume of IV fluid infusion- Intraoperative blood transfusion- Fluid balance (in and out difference)- Duration of operation (minute)- Main pancreatic duct diameter- Pancreas texture (soft, intermediate, hard)- Fistula risk score

After the operation the following parameters and events will be recorded:

- Capillary blood glucose levels (every 6 h for 5 consecutive days)- Any administration of insulin (for blood glucose ≥180 mg/dL)- Occurrence of a complication (90-days)- Type of complication- The complication burden according to CCI (90-day)- The severity of complication according to Clavien-Dindo classification- The need of reoperation, reason and postoperative day- The need of unplanned intensive care treatment and the duration (days)- The day of canalization to gas and stools- The day of resumption of oral feeding- The need and duration of artificial nutrition (for the control arm)- Potential hospital discharge according to predefined criteria- The actual day of hospital discharge- Disease staging- Readmission rate (30-day)- Mortality rate (90-day)

## Discussion

The use, timing of initiation, and route of delivery of artificial nutrition after PD is still a matter of debate for the conflicting evidence and the difference in study design. One randomized trial, showed that in patients submitted to PD and kept “nil by mouth” for 10 days after the operation, immediate parenteral feeding was associated with less complications when compared to progressive tube enteral nutrition (21) suggesting that the achievement of an immediate and full nutritional goal may be protective on the risk of morbidity. One systematic review (22) compared the outcomes of 5 feeding routes after PD and reported no difference in terms of safety and efficacy. A recent meta-analysis by Tanaka et al. (23) advocated that routine enteral nutrition after PD was associated with a lower incidence of infectious complications and a shorter length of hospital stay than non-enteral nutrition. Percutaneous tube feeding had a lower incidence of infectious complications and a shorter hospital stay than parenteral nutrition whereas naso-jejunal tube feeding was not associated with better postoperative outcomes. Thus, the authors concluded that as a supplement to regular oral diet, routine enteral nutrition, especially *via* a percutaneous enteral tube, may improve postoperative outcomes after PD.

The results of another randomized controlled trial (RCT) (24) on patients who underwent pylorus-preserving PD suggested additional early tube enteral nutrition did not affect the frequency of DGE and did not offer any further clinical advantages over early oral feeding. However, in persisting DGE, better outcomes were achieved when artificial nutrition, either parenteral or enteral, was started within 10 days of operation (25).

After the development of a clinically relevant pancreatic fistula, the use of enteral tube feeding was not superior to oral nutrition in terms of 30-day fistula closure rate. Compared with enteral feeding, oral feeding significantly reduced hospital costs and duration of stay (26).

Despite not specifically designed for patients undergoing PD, two recent large RCTs provided conflicting results on the need of early artificial nutritional support after major abdominal surgery. Zhang et al. (27) randomized patients at high nutritional risk, to immediate vs. gradual advancement to goal of enteral tube nutrition. The first group received 100% of the caloric requirement on postoperative day 3, while the other received 40% progressing to 80% of target on day 7. The results showed that immediate enteral feeding was non-inferior to gradual advancement in regards to infectious complications. However, immediate feeding was associated with more gastrointestinal intolerance events. The other trial (28) randomized 230 patients at high nutritional risk and poor tolerance to tube enteral nutrition, to receive supplemental PN early (on day 3) or late (on day 8) after surgery. The early group had significantly fewer nosocomial infections compared with the late group (8.7% vs. 18.4%; *p* = 0.04). No significant differences were found between the early and late group in the number of noninfectious complications. The authors concluded that early supplemental PN appeared a favorable strategy for patients with high nutritional risk and poor tolerance to EN.

In 2022, Joliat et al. (29) published the protocol of a multicenter, open-label, RCT for patients undergoing PD with a nutritional risk screening ≥3 in a setting of full ERAS strategy. Patients will be randomized to receive either early enteral nutrition (intervention group) or oral nutrition (control group) after the operation. Patients in the intervention group will receive tube enteral nutrition since the first night of the operation and the infusion will be increased daily if tolerated. The primary outcome will be the CCI at 90 days after surgery.

Differently from the above study design, we opted for parenteral nutrition instead of enteral tube feeding. The rational of giving parenteral feeding has been based on the ability of this therapy to provide the exact amount of calories and protein since the very beginning of administration. As opposite, tube enteral nutrition needs at least 4/5 days to reach the caloric target or even more depending on tolerance (30).

These two upcoming trials will allow to establish if early postoperative artificial nutritional support after PD may improve postoperative outcomes compared to oral nutrition alone within an established ERAS program. Moreover, the results might be useful for a potential updated version of the International Study Group on Pancreatic Surgery recommendations (7) on nutritional therapy in pancreatic surgery.

